### Prohibited Concomitant Medications

During the screening period and throughout the trial, subjects are prohibited from using the following medications:

- Any other antitumor drugs (chemotherapy, immunotherapy) except for the investigational drug;
- Radiation therapy;
- Medications that prolong the QT interval;
- Other investigational therapeutic agents.

## Definition of DLT

Any drug-related toxicity occurring within 25 days after the first dose of the investigational drug, as defined by CTCAE version 5.0, that is considered related to the investigational drug (including definitely related, probably related, or possibly related) will be regarded as a DLT:

1. Hematologic Toxicity

- Grade 3 febrile neutropenia, defined as an absolute neutrophil count (ANC) < 1.0 × 10^9^/L accompanied by fever, with a temperature > 38.3℃, or a temperature sustained ≥ 38.0℃ for more than 1 hour;
- Grade 4 neutropenia without fever lasting ≥ 5 days;
- Grade 3 thrombocytopenia (25×10^9^/L < platelet count≤50×10^9^/L) accompanied by bleeding of Grade 2 or higher according to the WHO bleeding classification (2017 revised version), or Grade 4 thrombocytopenia lasting≥7 days with platelet transfusion treatment occurring≥2 times (excluding acute leukemia patients).

1. Any Grade 3 or higher non-hematologic toxicity, including but not limited to:

- Grade 3 or higher QT interval prolongation;
- Hepatic toxicity: If the baseline levels of ALT, AST, or TBIL for the subject are ≤ Grade 1, then drug-related Grade 3 toxicity will be considered as DLT.

**The following situations are excluded:**

- Grade 3 fatigue, weakness, or fever;
- Grade 4 infusion reactions;
- Grade 3 controllable hypertension (systolic blood pressure ≥ 160 mmHg or diastolic blood pressure≥100 mmHg);
- Grade 3 nausea or vomiting lasting less than 72 hours, with adequate antiemetic and supportive treatment provided;
- Grade 3 diarrhea lasting less than 72 hours, with adequate antidiarrheal and supportive treatment provided;
- Grade 3 or 4 electrolyte abnormalities that can improve to Grade 2 or lower within 72 hours;
- Hair loss.

1. Patients with Acute Leukemia

- Persistent pancytopenia lasting > 42 days, accompanied by bone marrow hypoplasia (bone marrow cellularity < 5%) and the absence of leukemic cells in peripheral blood and bone marrow, will be considered a dose-limiting toxicity (DLT) due to bone marrow suppression. Pancytopenia is defined as leukocyte count < 4.0 × 10^9^/L, hemoglobin < 100 g/L, and platelet count < 100 × 10^9^/L.
- If the investigator cannot attribute any of the following events to a clearly identifiable cause (such as tumor progression, underlying or concurrent diseases, or concomitant medications), these events will be considered dose-limiting toxicities: hematologic toxicities possibly related to the study drug, grade 3 or higher non-hematologic toxicities, with the following exceptions:
- Alopecia
- Grade 3 fatigue, weakness, anorexia, fever, or constipation
- Grade 3 nausea, vomiting, or diarrhea that does not require tube feeding, intravenous nutritional support (TPN), or hospitalization
- Infections, bleeding, or other expected direct complications caused by underlying active leukemia

1. Others: Significant medical events deemed by the investigator to be possibly related to the study drug and discussed with the sponsor may be considered dose-limiting toxicities (DLT).
2. Any grade 5 adverse events.
3. Participants who have not recovered from toxicity and have interrupted treatment for more than 14 days (excluding interruptions greater than 14 days due to hematologic toxicity in acute leukemia).

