| **DLT definition** | According to NCI-CTCAE version 5.0, any of the following toxicities related to the study drug (including definitely related, probably related, or possibly related) that occur within 25 days after the first administration of the drug (during Phase 1 and Phase 2 of the trial) may be considered a dose-limiting toxicity (DLT):   1. Hematological toxicity;  - Grade 3 febrile neutropenia is defined as an absolute neutrophil count (ANC) of < 1.0×10^9^/L accompanied by fever, with a temperature > 38.3℃, or a temperature sustained at≥38.0℃for more than 1 hour; - Grade 4 neutropenia without fever lasting for ≥ 5 days; - Grade 3 thrombocytopenia (25×10^9^/L < platelet count≤50×10^9^/L) accompanied by bleeding classified as Grade 2 or higher according to the WHO bleeding classification (2017 revised edition), or Grade 4 thrombocytopenia lasting≥7 days that requires platelet transfusion treatment≥2 times (excluding patients with acute leukemia);  1. Any non-hematological toxicity of Grade 3 or higher, including but not limited to:  - Grade 3 or higher QT interval prolongation; - Hepatotoxicity: If the baseline levels of ALT, AST, or TBIL in the subjects are≤ Grade 1, then drug-induced Grade 3 toxicity will be considered a dose-limiting toxicity (DLT).   **Except for the following:**   - Grade 3 fatigue, weakness, fever; - Grade 4 infusion reaction; - Grade 3 controlled hypertension (systolic blood pressure≥160 mmHg, diastolic blood pressure≥100 mmHg); - Grade 3 nausea and vomiting lasting less than 72 hours, with adequate antiemetic medication and other supportive treatment; - Grade 3 diarrhea lasting less than 72 hours, with adequate antidiarrheal medication and other supportive treatment; - Grade 3-4 electrolyte abnormalities that improve to Grade 2 or lower within 72 hours; - Alopecia;  1. Acute leukemia patients  - Persistent pancytopenia lasting > 42 days, accompanied by bone marrow hypoplasia (bone marrow cells < 5%) and the absence of leukemic cells in peripheral blood and bone marrow, will be considered a dose-limiting toxicity (DLT) due to bone marrow suppression. Pancytopenia is defined as white blood cells < 4.0 × 10^9^/L, hemoglobin < 100 g/L, and platelets < 100 × 10^9^/L. - If the investigator cannot attribute any of the following events to a clearly identifiable cause (such as tumor progression, underlying or concurrent diseases, or concomitant medications), these events will be considered dose-limiting toxicities: hematological toxicities potentially related to the study drug, Grade 3 or higher non-hematological toxicities, with the following exceptions: - Alopecia - Grade 3 fatigue, weakness, anorexia, fever, or constipation - Grade 3 nausea, vomiting, or diarrhea that does not require nasogastric feeding, parenteral nutrition (TPN), or hospitalization - Infections, bleeding, or other expected direct complications caused by underlying acute leukemia  1. Other: Important medical events that the investigator believes cannot be ruled out as related to the study drug may be considered dose-limiting toxicities (DLT) after discussion with the sponsor. 2. Any Grade 5 adverse events. 3. Treatment interruption >14 days due to unresolved toxicity (excluding cases of acute leukemia where treatment is interrupted for more than 14 days due to hematological toxicity). |

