### Escalation Process

The trial begins with a low dose, enrolling 3-6 subjects in each dose group. The decision to proceed to the next dose group will be based on whether at least 3 evaluable subjects from the previous dose group experience Dose Limiting Toxicity (DLT) and the corresponding safety data within 25 days after the first administration. An evaluable subject is defined as one who has received ≥80% of the planned dose or has experienced DLT after at least one dose

The specific regulations for dose escalation are as follows:

Table 8 Dose Escalation Rules

| **Occurrence of DLT** | **Actions** |
| --- | --- |
| No DLT observed | Proceed to the next dose group |
| 1 DLT observed among 3 subjects | Recruit an additional 3 subjects to receive the same dose of the investigational drug and observe for DLT |
| 1 DLT observed among 6 subjects | Proceed to the next dose group |
| ≥2 DLTs observed among 3 or 6 subjects | Reduce to the previous dose group.   - If there are fewer than 6 evaluable subjects in the previous dose group, recruit an additional 3 subjects to reach a total of 6 evaluable subjects. If no more than 1 DLT is observed among the 6 evaluable subjects, terminate the trial, and that dose group will be considered the MTD. - If there are already 6 evaluable subjects in the previous dose group, terminate the trial, and that dose will be considered the MTD. |

**Enrollment Sequence for Subjects in the Same Dose Group:** At the beginning of each dose group, only 1 subject will be enrolled to observe the tolerability and safety of that subject within 25 days after the first administration.

- Only if this subject does not experience DLT can the remaining 2 subjects in the same dose group be enrolled simultaneously.
- If this subject experiences DLT, enrollment of the third subject can only occur after the second subject has completed the 25-day observation period following the first administration, and only if the second subject has not experienced DLT.

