**2）Dose Reduction and Treatment Interruption**

If a subject experiences a dose-limiting toxicity (DLT) during the single-dose or multiple-dose phases, treatment must be interrupted until the toxicity recovers to Grade 1 or below. Based on the investigator's judgment that the subject may benefit from continued treatment, the subject may resume medication.

In the continuation dosing phase, the dose may be adjusted or treatment may be interrupted according to the following rules:

| **Toxicity** | **CTCAE Grade** | **Measures** |
| --- | --- | --- |
| Nausea and vomiting | Grade 3-4 | If it occurs for the first time, consider using antiemetics for treatment and interrupt the medication until the toxicity recovers to Grade 1 or below. Continue treatment with the original dose, and it is recommended to use antiemetics as a preventive measure.  If it occurs again, interrupt the medication until recovery to Grade 1 or below, and reduce the dose to the previous level. |
| Diarrhea | Grade 3 | If it occurs for the first time, consider using antidiarrheal medication for treatment and interrupt the medication until the toxicity recovers to Grade 1 or below. Continue treatment with the original dose, and it is recommended to use antidiarrheal medication as a preventive measure.  If it occurs again, interrupt the medication until recovery to Grade 1 or below, and when resuming treatment, reduce the dose to the previous level. |
|  | Grade 4 | If it occurs for the first time, consider using antidiarrheal medication for treatment and interrupt the medication until the toxicity recovers to Grade 1 or below. Adjust the dose to the previous level for treatment, and it is recommended to use antidiarrheal medication as a preventive measure.  If it occurs again, discontinue treatment and withdraw from the study. |
| Neutropenia | Grade 3 | ANC: 0.75 - 1.0 × 10^9^ /L, maintain the current dose and continue treatment. ANC: 0.5 - 0.75 × 10^9^ /L, interrupt treatment until ANC recovers to 1.0 × 10^9^ /L, then continue treatment at the original dose. |
| Febrile neutropenia | Grade 3 | Interrupt treatment until ANC recovers to 1.0 × 10^9 /L; when resuming treatment, reduce the dose to the previous level. |
| Thrombocytopenia | Grade 3 | Maintain the current dose of treatment and monitor platelet counts weekly |

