## Concomitant Medication

### Permitted Concomitant Medications

From the date of signing the informed consent form, any concomitant treatments or changes in concomitant medications that subjects must receive during the trial must be recorded by the investigator in the corresponding section of the eCRF, including the drug name, dosage, administration times, and indications.

During the screening period and throughout the trial, subjects are allowed to use the following medications:

- Supportive treatment for tumors and adverse events occurring during the trial, such as antibiotics, antiemetics, antidiarrheals, antipyretics, antihistamines, analgesics, medications to increase white blood cell counts, and medications to control high white blood cell counts (e.g., hydroxyurea), etc.;
- Corticosteroids: prednisone < 20 mg/day or equivalent doses of other corticosteroids for the treatment of conditions unrelated to the disease under study; if using prednisone > 20 mg/day or equivalent doses of other corticosteroids, the duration should not exceed 4 days for the prevention or treatment of adverse events occurring during the trial (e.g., infusion reactions);
- Others: Baseline medications for concomitant conditions such as hypertension or diabetes that the investigator deems will not affect the observation of study endpoints and can be used concomitantly.

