### Assessment of Adverse Event Severity

Adverse events will be categorized using the Medical Dictionary for Regulatory Activities (MedDRA) classification system. Investigators must grade each adverse event according to its severity based on the CTCAE version 5.0. If the severity of an individual adverse event is not graded in the text, the investigator may use their medical judgment to assign a grade based on the levels defined by CTCAE (ranging from Grade 1 to Grade 5).

Table 10 NCI-CTCAE Adverse Event Grading

| Grading | Description |
| --- | --- |
| Grade 1 | Mild; asymptomatic or mild symptoms; clinical or diagnostic observations only; intervention not indicated. |
| Grade 2 | Moderate; minimal, local, or non-invasive intervention indicated; age-related instrumental activities of daily living are limited. |
| Grade 3 | Severe or medically significant but not immediately life-threatening; hospitalization or prolongation of existing hospitalization indicated; disabling; limitations in activities of daily living. |
| Grade 4 | Life-threatening; urgent intervention indicated. |
| Grade 5 | Death |

Note: *Instrumental Activities of Daily Living (IADLs) refer to tasks such as cooking, shopping for groceries or clothing, using the telephone, managing finances, etc.
**Activities of Daily Living (ADLs) refer to tasks such as bathing, dressing and undressing, eating, toileting, and taking medications, as opposed to being bedridden.

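### Outside acute leukaemia, two DLT rules reverse severity: Grade 4 infusion reactions are excused while Grade 3 count, and Grade 4 thrombocytopenia with bleeding is harder to count than Grade 3

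*Protocol*

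**What the plan says.** Section 3.4 of the protocol makes the following a DLT when related to the drug and occurring within 25 days of the first dose: "Any Grade 3 or higher non-hematologic toxicity, including but not limited to" QT prolongation and hepatic toxicity. The list of exclusions that follows contains "Grade 4 infusion reactions". Grade 3 infusion reactions are not on that list. The synopsis has the same entry, "Grade 4 infusion reaction". Table 10 in Section 8.1.2 describes Grade 4 as "Life-threatening; urgent intervention indicated".

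The haematologic part of Section 3.4 has two platelet limbs, neither of which applies to acute leukaemia:
- Grade 3 (above 25 and up to 50 × 10⁹/L) with bleeding of WHO Grade 2 or more. There is no duration or transfusion condition.
- Grade 4 lasting at least 7 days with at least 2 platelet transfusions. Bleeding is not a route.

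The DLT label drives the rest of the design. Table 8 in Section 3.2.4 sets the escalation step from the DLT count, and Section 3.5 defines the MTD by at most 1 DLT in 6 subjects. The enrolment sequence within a cohort also depends on it: "Only if this subject does not experience DLT can the remaining 2 subjects in the same dose group be enrolled simultaneously"; otherwise "enrollment of the third subject can only occur after the second subject has completed the 25-day observation period". Section 3.2.5 adds: "If a subject experiences a dose-limiting toxicity (DLT) during the single-dose or multiple-dose phases, treatment must be interrupted".

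**The concern.** A toxicity rule should be monotone: if the milder form of an event counts, the more severe form must count too. Both rules fail this. DLT is the primary safety endpoint, and the failure is in the unsafe direction, because the more severe event is the one that can go uncounted. The drug is given as a 30-minute infusion and Section 3.3.1 gives infusion reactions as an example of an event needing corticosteroids. Thrombocytopenia and haemorrhage are both on the anticipated-event list in Section 8.3.1. At stake are the escalation decision, the stagger between the first subject and the next two, and the declared MTD.

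**Working it through.** **1. The rules applied literally (subjects without acute leukaemia, event related to the drug)**

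| Event | DLT? | Reason |
| --- | --- | --- |
| Infusion reaction, Grade 3 | Yes | Grade 3 or higher, not excluded |
| Infusion reaction, Grade 4 | No | Expressly excluded |
| Infusion reaction, Grade 5 | Yes | Separate Grade 5 item |
| Platelets 40, WHO Grade 2 bleeding | Yes | Grade 3 bleeding limb |
| Platelets 10, WHO Grade 2 bleeding, 3 days, 1 transfusion | No | Fails both Grade 4 conditions |
| Platelets 10, WHO Grade 2 bleeding, 6 days, 3 transfusions | No | 6 days is less than 7 |

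The platelet gap has limits. Bleeding that is itself a CTCAE Grade 3 or higher event counts under the non-haematologic rule. An interruption of more than 14 days for unresolved toxicity also counts. What remains is bleeding such as WHO Grade 2 lasting under 24 hours with no red-cell transfusion, alongside Grade 4 platelets that do not meet both the 7-day and the 2-transfusion conditions.

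**2. When the subject stays in the denominator**

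Section 3.2.4 calls a subject evaluable after at least 80% of the planned dose, or after a DLT. There are four equal planned doses (D1, D8, D11, D15). One missed dose gives 3/4 = 75%, which is not evaluable. A subject with an uncounted event is therefore evaluable if all doses are still given or the event comes at or after D15. If 80% means cumulative amount, the threshold is 0.8 × 4 = 3.2 doses. A reaction during the D15 infusion then leaves the subject evaluable once 0.2 × 50 mL = 10 mL has been given.

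**3. Effect on Table 8 of one uncounted event in an evaluable subject**

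| Count with the event | Step | Count without it | Step |
| --- | --- | --- | --- |
| 1/3 | Add three subjects | 0/3 | Move up |
| 2/6 | Step down | 1/6 | Move up |

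**4. Effect on the stagger**

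If the first subject of a cohort has a Grade 3 infusion reaction, the third subject waits until the second has finished 25 days without a DLT. If the first has a Grade 4 reaction, the literal text lets subjects two and three start together.

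**5. Replacement**

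A subject who leaves the study within 25 days because of a Grade 4 infusion reaction leaves for a reason that is, by definition, not a DLT. Section 4.7 then allows replacement, and the event drops out of the DLT count.

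**6. Illustration with assumed rates**

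The protocol gives no DLT rate and no share of uncounted events, so both are assumptions here, and every subject is taken as evaluable. With true rate p and uncounted share s, the counted rate is q = p(1 − s). The probability of moving up is (1 − q)³ + 3q(1 − q)²(1 − q)³.

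| p | s = 0 | s = 10% | s = 25% | s = 50% |
| --- | --- | --- | --- | --- |
| 0.33 | 0.43 | 0.50 | 0.61 | 0.78 |
| 0.40 | 0.31 | 0.38 | 0.49 | 0.71 |
| 0.50 | 0.17 | 0.23 | 0.35 | 0.60 |

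Check for p = 0.40, s = 0: 0.6³ + 3 × 0.4 × 0.6² × 0.6³ = 0.216 + 0.093 = 0.309.

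**The case against.** The best case for the plan is that it does not rest on the label alone. Tolerability and pharmacokinetic results (Section 3.1) and safety data (Section 3.2.4) also inform the decision to escalate. The residual clause in Section 3.4 lets an important event be named a DLT after discussion with the sponsor. A subject enters the multiple-dose phase only if treatment was well tolerated (Section 6.3). The investigator may adjust or interrupt dosing for any adverse event (Section 8.1.4), and infusion rate and duration can be changed (Section 5.4). Infusion reactions are not on the anticipated-event list, and the Grade 4 entry may be a slip for Grade 3.

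Much of this stands as regards the care of the individual subject. It does not repair the count: the residual clause is permissive, and Section 3.5 reads only DLTs. A slip that appears in both places, with nothing correcting it, will be applied as written.

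Four stronger readings are tempting, and the protocol does not support them.
- *That Grade 4 infusion reactions are excused in everyone.* The acute-leukaemia rules have their own exception list, which omits infusion reactions, so such a reaction may still count there.
- *That one missed dose makes a subject replaceable.* Section 4.7 covers subjects who discontinue the study. A subject at 75% who stays on study is not evaluable, but Section 4.7 does not name that case.
- *That the instruction in Section 8.4 to suspend dosing when bleeding occurs would systematically remove the platelet cases.* That sentence sits in a paragraph that opens with multiple myeloma.
- *That the leukaemia criterion of pancytopenia beyond 42 days can never be read before a cohort decision.* With onset on D1 it is met on D43. The first subject's 25 days must pass before the next two enrol, so the cohort decision falls at about that subject's D50 (25 + 25). Occurrence within 25 days can also be read as onset, and the next leukaemia item already counts unattributed haematologic toxicity. The criterion fits the 25-day window poorly, but this is only a side note.

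**Conclusion.** The concern holds for subjects without acute leukaemia. As written, Section 3.4 and the synopsis count a Grade 3 infusion reaction and excuse a Grade 4 one. They also count Grade 3 thrombocytopenia with WHO Grade 2 or higher bleeding at any duration, while holding Grade 4 thrombocytopenia with the same bleeding to a 7-day, 2-transfusion test.

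The size is one step of Table 8 per uncounted event in an evaluable subject, plus loss of the stagger after a Grade 4 reaction in the first subject. A reader might infer that escalation would go ahead automatically or that an unsafe MTD is likely. The protocol supports neither: other safety data are reviewed, discretion may rescue a case, and the frequency of these events cannot be derived. The probabilities in the illustration are conditional on assumed rates. The conclusion rests on the literal text and not on those rates.

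**What to change.** Amend Section 3.4 and the synopsis together.
- Count Grade 4 infusion reactions as DLTs, and limit any infusion-reaction exclusion to Grade 3 or lower.
- Reword the first platelet limb as *Grade 3 or higher thrombocytopenia with WHO Grade 2 or higher bleeding*. Keep the 7-day, 2-transfusion limb for Grade 4 thrombocytopenia without such bleeding.

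The cost is one text amendment, with no new visits, no extra scheduled blood counts and no longer DLT window. Slightly more DLTs may be counted, so some cohorts may expand to six or stop one level earlier.

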| **Safety assessments** | - Dose limiting toxicity (DLT); - Maximum tolerated dose (MTD); - According to CTCAE version 5.0, the types, severity, incidence, timing, duration, and relationship to the investigational drug of adverse events; - Vital signs: including temperature, heart rate, respiratory rate, and blood pressure (systolic and diastolic); - Physical examination: including examination of the skin, mucous membranes, lymph nodes, head, neck, chest, abdomen, spine/extremities, and nervous system - Laboratory tests: - Complete blood count: red blood cell count, hemoglobin, platelet count, white blood cell count, neutrophil count, and lymphocyte count; - Urinalysis: urine protein, urine red blood cells, and urine white blood cells; - Blood biochemistry: blood creatinine, urea, total bilirubin, alanine aminotransferase (ALT), aspartate aminotransferase (AST), alkaline phosphatase, total protein, albumin, electrolytes (K^+^, Na^+^, Ca2^+^, Mg^2+^, Cl^-^), total cholesterol, low-density lipoprotein (LDL), high-density lipoprotein (HDL), creatine kinase (CK), creatine kinase isoenzyme (CK-MB), α-hydroxybutyrate dehydrogenase (α-HBDH), lactate dehydrogenase, and fasting blood glucose; - Coagulation: PT, APTT, TT, FIB; - 12-lead ECG: PR interval, QRS interval, QT interval, QTc interval; - Echocardiogram (this examination may be performed if symptoms such as precordial pain or palpitations occur, or if the investigator deems it necessary); - Imaging assessments (CT or PET-CT or whole-body X-ray); |
| **Pharmacokinetic evaluation** | Single-Dose Phase：T_max_, C_max_, AUC_(0-t)_, AUC_(0-∞)_, V_d_, Ke, t_1/2_, MRT, CL  Multiple-Dose Phase：T_max_, C_ss_min_, C_ss_max_, C_ss_av_, t_1/2_, CL, AUC_ss_ |
| **Biomarker** | The acetylation levels of histones H3 and H4 are to be measured exclusively in leukemia patients. |
| **Evaluation of efficacy** | Assess the clinical efficacy of the drug in subjects before treatment and after multiple doses according to the evaluation criteria for different hematological malignancies.   - Objective mitigation rate (ORR) - Progression free survival (PFS) - Disease Control Rate (DCR): This refers to the proportion of patients in whom the tumor has reduced in size or remained stable for a certain period of time, including cases of complete remission (CR), partial remission (PR), and stable disease (SD). |

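### Read literally, the acute-leukaemia DLT bullet counts a low-grade or brief cytopenia with no other clear cause as a DLT; it should point to item 1's graded criteria

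*Protocol*

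**What the plan says.** The acute-leukaemia part of Section 3.4 (Definition of DLT) has two bullets. The first is pancytopenia lasting more than 42 days with a hypoplastic, leukaemia-free marrow. The second opens "If the investigator cannot attribute any of the following events to a clearly identifiable cause" and then names as DLTs "hematologic toxicities possibly related to the study drug, grade 3 or higher non-hematologic toxicities, with the following exceptions". The synopsis reads "hematological toxicities potentially related to the study drug, Grade 3 or higher non-hematological toxicities, with the following exceptions". In both places the bullet says that these events will be considered DLTs; only the synopsis lead-in to the whole definition says may. No exception in the bullet's list covers a mild or short drug-related cytopenia. The nearest covers complications of the leukaemia itself.

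Item 1 of the same section gives the general haematologic criteria:
- febrile neutropenia;
- "Grade 4 neutropenia without fever lasting ≥ 5 days";
- Grade 3 thrombocytopenia with WHO Grade 2 or higher bleeding;
- Grade 4 thrombocytopenia for at least 7 days "with platelet transfusion treatment occurring≥2 times (excluding acute leukemia patients", after which the bracket closes.

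The last item of the DLT list counts treatment interruptions beyond 14 days, but "excluding interruptions greater than 14 days due to hematologic toxicity in acute leukemia". In Table 8 (Section 3.2.4), two or more DLTs among three or six subjects lead to "Reduce to the previous dose group".

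**The concern.** In leukaemia, a DLT rule for blood counts would normally be more lenient than in lymphoma or myeloma, and the protocol's explicit leukaemia carve-outs go that way. This bullet goes the other way. As written it has no floor. It would also take in lymphopenia and anaemia, for which item 1 has no criterion at all.

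All diseases share one DLT count per dose group, and that count decides the MTD, which is a primary objective. One such event in the first three subjects forces expansion to six. Two events, or one plus a true DLT, force a step down. If the dose was in fact tolerable, the MTD is then declared one level too low. The error is conservative for safety: it does not lead to a more toxic dose.

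**Working it through.** **1. Setting the provisions side by side.**

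| Place | What it requires | Fit with the literal bullet |
|---|---|---|
| 3.4, item 1 | A grade plus fever, bleeding or a duration | Bullet has none of these |
| 3.4, leukaemia carve-outs | Grade 4 thrombocytopenia limb and haematologic interruptions beyond 14 days do not count | Bullet is stricter, not more lenient |
| 3.4, first leukaemia bullet | Pancytopenia beyond 42 days | Largely redundant if any drug-related cytopenia counts |
| 3.2.5 | After a DLT, interrupt until Grade 1 or below | No meaning for a Grade 1 event |
| 8.4 | No regimen change for Grade 1–3 neutropenia | A literal DLT would require interruption |

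Example: inclusion criterion 5 requires neutrophils of at least 1.5 and platelets of at least 75 ×10⁹/L, with no exemption for leukaemia. Appendix 14.3 puts the Grade 1 floor at those same values. A fall in neutrophils to 1.4 with no other clear cause would be a DLT in a leukaemia subject. In a lymphoma subject, afebrile neutropenia counts only at Grade 4 for at least 5 days.

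**2. Effect on Table 8, if the bullet is applied literally.** The plan gives no figure to reproduce. Assumed inputs:
- q: 25-day probability of a low-grade cytopenia that survives the attribution condition;
- t: true DLT probability;
- the number of leukaemia subjects in each three.

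A leukaemia subject has DLT probability pL = 1 − (1 − t)(1 − q); the others have t. With X1 and X2 the DLT counts in the first and second three:

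stop = P(X1 ≥ 2) + P(X1 = 1) × P(X2 ≥ 1); expand = P(X1 = 1).

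*One leukaemia subject in each three, t = 0.* Only that subject can have an event, so expand = q and stop = q × q:
- q = 0.05: 0.0025
- q = 0.2: 0.04
- q = 0.3: 0.09
- q = 0.5: 0.25

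*Leukaemia only in the first three, one event at most, t = 0.* P(X2 ≥ 1) = 0, so stop = 0.

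*t = 0.10.* Without the bullet (q = 0): 0.028 + 0.243 × 0.271 = 0.094. For q = 0.2, pL = 1 − 0.9 × 0.8 = 0.28. Then P(X1 = 0) = 0.72 × 0.81 = 0.583, P(X1 = 1) = 0.28 × 0.81 + 0.72 × 0.18 = 0.356, and P(X1 ≥ 2) = 0.060.
- One in each three: 0.060 + 0.356 × 0.417 = 0.209.
- First three only: 0.060 + 0.356 × 0.271 = 0.157.

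The same steps for q = 0.05 (pL = 0.145; probabilities 0.693, 0.271, 0.036) give 0.036 + 0.271 × 0.307 = 0.120 and 0.036 + 0.271 × 0.271 = 0.110. For q = 0.5 (pL = 0.55; 0.3645, 0.5265, 0.109) they give 0.109 + 0.5265 × 0.6355 = 0.444 and 0.109 + 0.5265 × 0.271 = 0.252.

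*Random composition, t = 0.* If each subject has leukaemia with assumed probability f, the per-subject rate is p = f × q. At f = 1/3, q = 0.5, p = 1/6: 0.074 + 0.347 × 0.421 = 0.220. At f = 0.2, q = 0.05, p = 0.01: 0.0003 + 0.0294 × 0.0297 = 0.0012.

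**3. Cost of one level (Table 7).** 1 − 1.2/2.4 = 50% at the bottom; 1 − 8.4/11.2 = 25% and 1 − 11.2/15 = 25% at the top.

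**The case against.** The strongest reply is that the literal reading is not the intended one. Items 1 and 2 of Section 3.4 are haematologic toxicity and then Grade 3 or higher non-haematologic toxicity, and the leukaemia bullet names the same two categories in the same order. It can be read as carrying items 1 and 2 over to leukaemia, with an attribution condition and its own exceptions. The clashes with Sections 3.2.5 and 8.4 support that reading, since an investigator applying the whole protocol would hardly call a neutrophil count of 1.4 dose-limiting. This largely stands: the rival reading is plausible and probably what was meant. But no text says so, the bullet says will be considered in both places, and a primary-endpoint definition should not rest on inference.

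The second reply is that attribution removes most events, because underlying disease is a named cause and these are relapsed or refractory patients. That also stands in part, and it is why q must be allowed to run towards 0. It does not close the gap. The condition needs a clearly identifiable cause, and subjects enter with near-normal neutrophils and platelets and no recent transfusion, so a new fall is not automatically explained by leukaemia.

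A reader might infer that leukaemia subjects must appear in every dose group, because "The acetylation levels of histones H3 and H4 are to be measured exclusively in leukemia patients" while Section 10.7 describes acetylation for each dose group. The documents set no quota, so that composition is an assumption.

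**Conclusion.** The bullet is wrong as written and contradicts other parts of the protocol, but the remedy is a clarification. Literal application would let ungraded cytopenias into the count that sets the MTD, and the error would be conservative.

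Its size cannot be derived from the documents. With one leukaemia subject in each three and no true DLTs, the false-stop risk is q²: near 0 at small q and 25% at q = 0.5. It is 0 if leukaemia subjects fall only in the first three and contribute at most one event. With an assumed true DLT rate of 10%, the stop risk moves from 9% to between 11% and 44%, depending on q (0.05 to 0.5) and on where leukaemia subjects fall.

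A reader might take the upper figures as the expected effect, or conclude that the MTD will be set too low. The documents support neither. Those figures need a high q after attribution, a leukaemia subject in both threes, and investigators who apply the literal text. The 25% to 50% understatement of dose applies only if a tolerable dose is stopped.

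**What to change.** In Section 3.4 and the synopsis, replace the ungraded phrase with: *haematologic toxicities meeting the grade and duration criteria of item 1 (febrile neutropenia; Grade 4 neutropenia lasting at least 5 days; Grade 3 thrombocytopenia with WHO Grade 2 or higher bleeding)*. Keep the attribution condition. Keep the Grade 4 thrombocytopenia limb excluded for acute leukaemia, as item 1 already has it. State whether that exclusion covers only the Grade 4 limb or the Grade 3 bleeding limb as well, since the bracket can be read either way; if both, drop the bleeding criterion from the new wording.

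The cost is one sentence in two places, by amendment. Fewer leukaemia cytopenias would count as DLTs than under the literal text. Timing a 5-day neutropenia needs counts between D15 and D25. Section 6.3 schedules none there, but item 1 already needs them, and Section 8.4 asks for counts about every two days in Grade 1–3 neutropenia. If any leukaemia DLT has already been counted under this bullet, reclassify it only against the amended criterion and document the change, because it alters primary-endpoint data.
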